### Randomisation

Randomisation will be undertaken using an online tool (www.randomizer.org) with a fixed block size of four to allocate participants on an individual basis at a ratio of 1:1 to the intervention (Frail-LESS) and control (continue with usual healthcare) groups. This approach will be used to increase the likelihood of balanced numbers in the trial arms. The randomisation will be conducted by a researcher independent from the study team. Researchers and participants will be blinded to group allocation until baseline measurements have been completed.

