### Study setting

This study will be conducted with community-dwelling older adults living in the London metropolitan area, England. Study measurements will be taken at Brunel University London or at participants’ homes depending on participant preference and ability to travel to the University campus. All components of the intervention will be delivered remotely.

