### Participant eligibility criteria

Screening for participant eligibility will be administered over the phone by a researcher with a clinical health professions background. Eligible participants for this study will be community-dwelling older adults aged ≥ 65 years living with very mild or mild frailty classified according to the Clinical Frailty Scale version 2.0 [33]. Very mild frailty describes people who are not dependent on others for daily help, but often have symptoms that limit activities; a common complaint is being “slowed up” and/or being tired during the day. Mild frailty describes people who have more evident slowing and need help in high order instrumental activities of daily living. Typically, mild frailty progressively impairs shopping and walking outside alone, meal preparation, and housework. Additional inclusion criteria are (1) participants spend the majority (> 60%) of the waking day sitting, measured via self-report using the International Physical Activity Questionnaire item (“During the last 7 days, how much time did you spend sitting on a week day?”) and (2) have a Functional Ambulation Category rating of ≥ 4, i.e. able to ambulate independently with or without a walking aid on level surfaces without supervision or assistance from another person [34].

Exclusion criteria include being unable to communicate in English to a level needed for effective engagement in the study, any physical or mental impairment affecting participants’ ability to stand and walk, and cognitive impairment (score ≥ 7 in the Six-Item Cognitive Impairment Test [35]).

Individuals who are identified as being eligible will be invited to provide written informed consent and to make an appointment to have baseline measures taken.

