
#### Intervention protocol

The Frail-LESS intervention will consist of tailored feedback, a psychoeducation workbook, a wearable device, health coaching and peer support, as described in detail below. Each participant randomised to the intervention group will receive the Frail-LESS intervention for 6 months. At the outset, participants will be posted an intervention pack consisting of a tailored feedback sheet, a psychoeducation workbook, a wearable device and accompanying user manual, an information sheet summarising the intervention (including contact details for their health coach), and information on how to join a peer support group. These materials (other than the workbook and wearable device) will also be emailed to each participant by a researcher. Specifically, the intervention components include the following:

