##### Peer support

Intervention participants will be provided with the opportunity to join a Frail-LESS peer support group. A monthly virtual meeting will be arranged by the research team and will be structured in a way that encourages the participants who opt to take part to discuss their experiences of the intervention, suggest and ‘try-out’ different activities that could be used to reduce and break up sitting, and offer general support to one another. A WhatsApp group will be created by one of the intervention participants to provide participants with the opportunity to interact with one another outside of the virtual meetings. Participants will be advised they can also exchange email addresses to communicate with one another if they wish to.

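### Fixed blocks of four let staff who know past allocations deduce up to one third of assignments, and stated blinding stops before the 3- and 6-month performance tests

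*Protocol article*

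**What the plan says.** All references are to the protocol article.

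- **Randomisation, method.** An online tool is used "with a fixed block size of four to allocate participants on an individual basis". The two arms receive equal allocation (1:1). No stratification is mentioned. The stated reason for blocking is to keep the arm sizes balanced.
- **Randomisation, concealment.** "The randomisation will be conducted by a researcher independent from the study team".
- **Randomisation, blinding.** In a separate, later sentence: "Researchers and participants will be blinded to group allocation until baseline measurements have been completed". No section states any blinding after that point.
- **Participant eligibility criteria.** "Screening for participant eligibility will be administered over the phone by a researcher with a clinical health professions background". Eligibility includes a Clinical Frailty Scale grade, which calls for judgement.
- **Intervention protocol.** Materials for the intervention arm "will also be emailed to each participant by a researcher".
- **Peer support.** For the intervention arm only, "A monthly virtual meeting will be arranged by the research team".
- **Study setting.** "All components of the intervention will be delivered remotely".
- **Study design; Sarcopenia.** Grip strength (repeated maximal attempts) and the SPPB are measured at baseline and again at 3 and 6 months. They are components of sarcopenia, the intended primary outcome of the full trial.

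**The concern.** When every block has four places, two per arm, the end of a block follows from its beginning. The independent randomiser keeps the list away from the team. That does not stop someone from working out the next allocation from the previous ones, and the blinding sentence opens each allocation to researchers as soon as that participant's baseline is done. A person who can foresee the next arm could, without intending to, be influenced when grading frailty, timing an enrolment or encouraging effort at baseline.

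The second issue is where the stated blinding stops. Participants in a behavioural trial cannot be blinded after allocation, but assessors can be. Grip strength and the SPPB respond to encouragement, and their follow-up measurements all fall after the stated blinding has ended.

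At stake are the group summaries of potential efficacy on sarcopenia and physical function, a secondary objective whose results are to inform the definitive trial. Descriptive analysis does not remove bias from a group mean.

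**Working it through.** **Inputs.** Block size 4, fixed, and 1:1 ratio, so two places per arm in each block (Randomisation). Target 40, 30% attrition, 60 to be recruited (Sample size).

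**The plan's own figure.** 40 / (1 − 0.30) = 57.1, so 58. The stated 60 is within two participants of this and equals 60 / 4 = 15 complete blocks. The article gives no figure for predictability.

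**Certain assignments with full knowledge of the block so far.** The six equally likely sequences are AABB, ABAB, ABBA, BAAB, BABA and BBAA. An assignment is certain once one arm's two places are used.

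- The 4th place is always certain: 1 per block.
- The 3rd place is certain only after AA or BB: 2 of 6 sequences, or 1/3 per block.
- Total: 1 + 1/3 = 4/3 per block; (4/3) / 4 = 33.3%; 15 × 4/3 = 20 of 60 expected.

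**Best guess with full knowledge.** The probability of a correct guess at places 1 to 4 is 1/2, 2/3, 2/3 and 1. The sum is 2.83, and 2.83 / 4 = 70.8%, against 50% by chance.

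**Effect of overlapping enrolments.** Eligibility is judged by phone before consent and a booked baseline visit. The seven-day activPAL wear follows that visit. Several participants may therefore be in the pipeline at once, with the latest allocations not yet known.

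- Latest one unknown: only the 4th place can be certain, and only if the first two match. That is 1/3 per block; (1/3) / 4 = 8.3%; 15 × 1/3 = 5 of 60.
- Latest two or more unknown: at most one earlier allocation in the block is known, so nothing is certain: 0%.

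**Effect of varying the block size.** This was simulated with 60 participants and 3,000 runs. The guesser knows the set of sizes and all past allocations, but not the order of the sizes.

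| Scheme | Certain assignments | Best guess correct |
|---|---|---|
| Fixed 4 (exact) | 33.3% (20 of 60) | 70.8% |
| Random 4 and 6 | 5.5% (about 3 of 60) | 69% |
| Random 2, 4 and 6 | 3.9% (about 2 of 60) | 70% |

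Varying the size removes nearly all the certainty. It hardly changes how often an informed guess is right.

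**Blinding set against the measurement schedule.** Stated blinding covers the period up to the end of baseline. Grip strength and the SPPB are repeated at 3 and 6 months. No section extends blinding to those visits or identifies the assessors.

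**The case against.** The strongest reply has four parts.

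1. *The one third is a ceiling.* It requires the block size, the block start and every earlier allocation in the block, all known when eligibility is judged. This stands, and the honest range is 0% to 33%. The article gives no recruitment dates, so it cannot be settled whether recruiters could read the block size in print while enrolling.
2. *The link between roles is not documented.* A reader might infer that the same people screen, enrol, measure and learn every allocation. The article refers only to a researcher or the research team at each step and never says that these are the same individuals. It shows that some team members learn the arms, not that the screener does.
3. *Unblinded follow-up is not stated.* A reader might take it as fact that follow-up assessors know the arm. The article does not say so. It is a reasonable inference from where the stated blinding ends, and no more. Sitting, standing and stepping are device-measured and muscle mass comes from bioimpedance, so the concern is confined to the effort-dependent tests.
4. *Little depends on it here.* The primary aim is feasibility, safety and acceptability, efficacy is summarised descriptively, and no progression criterion uses an efficacy estimate. This also stands and limits the importance of the point.

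What the reply does not remove is the design itself. The block size is small and does not vary, researcher blinding is stated to end participant by participant, and the independent randomiser gives no protection against deduction from past allocations.

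**Conclusion.** The point holds as a moderate one that is cheap to correct. Up to one third of assignments (at most about 20 of 60 expected) can be deduced with certainty, on the assumption that the block size, the block start and all earlier allocations in the block are known. If enrolments overlap so that the latest one or two allocations are unknown, the share is 8.3% (about 5 of 60) or 0%. Separately, grip strength and the SPPB at 3 and 6 months may be taken by someone who knows the arm, because the stated blinding has ended and nothing extends it.

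Both issues affect the exploratory efficacy summaries intended to inform the definitive trial. The documents do not support the stronger conclusion that the feasibility aims or the progression criteria are undermined.

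**What to change.** **Block size.** Use randomly varied block sizes, for example 2, 4 and 6, and withhold the sizes and their order from staff who screen and enrol. This cuts certain assignments from up to 33.3% to about 4%. Best-guess accuracy stays near 70%, so the gain lies in removing certainty. The cost is a new list and a slight possible imbalance: a block of six has three places per arm, so stopping inside one leaves the arms at most three apart.

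**Access to allocations.** Have the independent randomiser release each allocation only to staff who deliver the remote intervention.

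**Follow-up assessment.** Where existing staffing allows, have the 3- and 6-month physical measures taken by team members not told the allocation, and record any unblinding. Remote delivery makes this separation easier. The article gives no staffing numbers beyond the five coaches, so whether it needs extra people cannot be judged. Some unblinding by participants is likely, and the feedback sheets and the process-evaluation questions on intervention components should be handled by someone other than the assessor. If separation is not possible, state this and report grip strength and the SPPB as assessed unblinded. The cost is one paragraph on roles and some care in scheduling.

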### The Frail-LESS intervention

#### Intervention development

The Frail-LESS (LEss Sitting and Sarcopenia in Frail older adults) intervention was developed following Medical Research Council guidelines for developing and evaluating complex interventions [38]. The Behaviour Change Wheel (BCW), which has the COM-B (Capability, Opportunity, Motivation-Behaviour) system at its hub, was used as a framework enabling translation of a COM-B diagnosis to the design of an evidence-informed intervention [39, 40]. Barriers and facilitators for reducing and breaking up sitting were identified from a systematic review and thematic synthesis of older adults’ perceptions of sedentary behaviour, which included 351 participants across 15 medium or high quality studies [22]. These were mapped to the BCW intervention functions and the policy categories through which those functions would be supported. Next, the optimal behaviour change techniques (BCTs) [41] for reducing and breaking up sitting and their mode of delivery were identified. This approach to intervention development has been used in previous cost-effective interventions that significantly reduced sitting and improved cardiovascular health and psychological wellbeing in office workers in the short and long-term [42–45] and within a community setting [46]. The proposed intervention was then refined following consultation among the research team and with the Brunel Older People’s Reference Group taking into consideration the APEASE (Acceptability, Practicability, Effectiveness/cost-effectiveness, Affordability, Safety/side-effects, Equity) criteria [47] and the ability for the intervention to be delivered remotely. The mode of delivery of the BCTs in this intervention will include the use of tailoring and technology (as described below), which older adults most frequently identified as being suitable to support reductions in sedentary behaviour [22]. A meta-analysis also reported significant reductions in sedentary time and improvements in physical functioning in response to technology-delivered behaviour change interventions in older adults [48]. However, some older adults indicated that technology-based interventions may not be acceptable due to issues such as lack of familiarity or access to electronic devices or the internet [22]. It is therefore possible that the intervention evaluated in this study may only be representative of older adults who volunteer to take part in the study, and who are familiar with technology and/or willing to develop their competence.

#### Intervention protocol

The Frail-LESS intervention will consist of tailored feedback, a psychoeducation workbook, a wearable device, health coaching and peer support, as described in detail below. Each participant randomised to the intervention group will receive the Frail-LESS intervention for 6 months. At the outset, participants will be posted an intervention pack consisting of a tailored feedback sheet, a psychoeducation workbook, a wearable device and accompanying user manual, an information sheet summarising the intervention (including contact details for their health coach), and information on how to join a peer support group. These materials (other than the workbook and wearable device) will also be emailed to each participant by a researcher. Specifically, the intervention components include the following:

##### Tailored feedback

Each intervention participant will be provided with a personalised feedback sheet based on their sitting, standing and stepping measurements at each time point (i.e. baseline, 3 months and 6 months). This will include a graphical representation and written explanation of their daily sitting, standing, stepping and number of breaks from sitting.

##### Psychoeducation workbook

This paper-based workbook will cover information on the health risks of sitting too much, potential benefits of reducing and breaking up sitting, tasks for goal setting, action planning, identifying potential barriers to reducing and breaking up sitting, and examples of activities to reduce and break up sitting.

##### Wearable device

A Garmin Vivofit wrist-worn device (Garmin Ltd., Kansas, USA) will be accompanied by a guidance document for its use and the manufacturer’s manual. The Vivofit tracks inactive time, daily steps and daily energy expenditure (kcal). A coloured move bar fills up on the display with an audible alert if the user has been inactive for too long to prompt them to get up and ambulate for a few minutes so the bar can be reset. The user can choose to connect the device to a smartphone app to set their own personal step goals and visualise a wider array of activity-related data.

##### Health coaching

Individual health coaching sessions will be provided throughout the intervention by individuals trained in coaching for health specifically for this study. The health coaches will have backgrounds in health psychology and behaviour change. Training developed and led by [name] will cover how to identify influences on sitting behaviour in relation to capability, opportunity, and motivation to create a COM-B diagnosis [49, 50]. This will be facilitated with communication style motivational interviewing [51–53], and the GROW model of health coaching (GROW: goal, reality, options, will/way forward) [54]. Trained health coaches will follow the ‘engage, focus, evoke, plan’ strategy of motivational interviewing, with an emphasis on the consultation allowing partnership, acceptance, compassion, and evocation (PACE) [55]. Core communication skills to support an effective consultation [56, 57] will be used, such as the RULE (Resist the righting reflex; Understand client motivation; Listen; Empower) and the OARS (Open-ended questions, Affirmations, Reflective listening, Summaries), showing empathy, building rapport and rolling with resistance when needed. These will be linked to the delivery of relevant BCTs; this person-centred approach aims to increase self-determined capability, opportunity, motivation and ultimately behaviour. Health coaching sessions will take place 3 to 5 days after allocation to the intervention group followed by further sessions approximately 2, 6, 12, and 18 weeks after the intervention starts. Health coaching will take place via video call or telephone, based on participant preference.

##### Peer support

Intervention participants will be provided with the opportunity to join a Frail-LESS peer support group. A monthly virtual meeting will be arranged by the research team and will be structured in a way that encourages the participants who opt to take part to discuss their experiences of the intervention, suggest and ‘try-out’ different activities that could be used to reduce and break up sitting, and offer general support to one another. A WhatsApp group will be created by one of the intervention participants to provide participants with the opportunity to interact with one another outside of the virtual meetings. Participants will be advised they can also exchange email addresses to communicate with one another if they wish to.

### Control group

Individuals randomised to this group will continue with any usual healthcare that they may be receiving and not receive the Frail-LESS intervention. They will have the opportunity to receive tailored feedback based on their 6-month sitting, standing and stepping measurements, the psychoeducation workbook, wearable device and join the peer support group once the study has ended. Participants in this group will undergo the same set of measurements as the intervention group at all time points.

### Measurements

#### Trial feasibility outcomes

Feasibility outcomes will include participant eligibility, recruitment and retention rates for the trial. Data completion rates for the intended primary outcome in a future trial (sarcopenia) will also be assessed. Acceptability of the intervention to participants, intervention fidelity and adherence will be evaluated during the process evaluation as described below. Intervention safety will be evaluated in terms of pain (using a 100-mm visual analogue scale [58]) and fatigue (using the Fatigue Severity Scale [59]) in addition to frequency of falls, hospital admissions and adverse events at each data collection time point. Adverse events will also be recorded ad-hoc if reported by a participant.

#### Demographic information

At baseline, demographic data will be collected including age, sex, ethnicity, comorbidities, living alone/with others, access to a green space, type of home, stairs to home, employment status, and COVID-19 circumstances (vaccination status, shielding, history of COVID-19 diagnosis).

#### Expected outcomes for a full trial

The below measures will be collected at baseline and again approximately 3 months and 6 months after group allocation. A data collection session will be arranged to take physical measures at Brunel University London or at participants’ homes, depending on preference and participants’ ability to travel. All questionnaire outcomes will be completed online using Qualtrics (Qualtrics, London, UK) or on paper, depending on participant preference. If it is not possible to arrange a data collection session with a participant within 3 weeks of their expected measurement date for any specific time point (e.g. due to them being uncontactable or unavailable), the data will be considered unobtainable. Similarly, this would be the case if a participant misses two scheduled data collection sessions at any given time point.

#### Sarcopenia

Objectively assessed sarcopenia is the intended primary outcome for a full trial. This will be measured in line with the European Working Group on Sarcopenia in Older People guidelines [60]. Hand grip strength will be measured using a hand grip dynamometer (Takei Scientific Instruments Co., Ltd., Niigata, Japan) on the dominant hand whilst standing with the elbow fully extended. Participants will complete three maximum attempts with a 1-min rest between each and the average recorded [61]. The Bodystat 1500 (Bodystat Ltd., Isle of Man) bioelectrical impedance device will be used to estimate muscle mass to the nearest 0.1 kg. Participants will be required to fast for 4 h prior to this measurement, avoid exercise in the 12 h beforehand and avoid caffeine and alcohol for 24 h beforehand to increase validity of the data [62]. Individuals fitted with a pacemaker will be excluded from bioelectrical impedance measures. Physical performance will be measured using the Short Physical Performance Battery (SPPB), which includes standing balance, walking speed and rising from a chair [63]. Standing balance will be tested using side-by-side, semi-tandem and tandem stands in this order for 10 s each. An 8-foot walking course will be used to evaluate walking speed with participants instructed to “walk to the other end of the course at your usual speed, just as if you were walking down the street to go to the shop”. The walk will be timed and will be performed twice with the average time used for analysis. The rising from a chair task will be completed using a straight-backed chair placed next to a wall. Participants will fold their arms and be instructed to stand up once from the chair. If this is performed successfully, participants will be asked to stand up and sit down as quickly as possibly five times, which will be timed. Each of the SPPB tests are scored on a 0–4 scale following published guidelines [63].

In addition to objective measures, the SARC-F (strength, assistance with walking, rising from a chair, climbing stairs, and falls) questionnaire will be used for participants to self-report their ability to carry a heavy load, walking, rising from a chair, climbing stairs, and falls frequency [64]. The SARC-F has been validated for sarcopenia classification that has comparable predictive ability to international diagnostic criteria [60].

